## Abstract

**Background:**

Women experience greater difficulty achieving smoking abstinence compared to men. Recent evidence suggests that hormonal fluctuations during different phases of the menstrual cycle can contribute to lower smoking abstinence rates following a quit attempt among women. However, these findings are limited by small sample sizes and variability among targeted smoking quit dates. This clinical trial aims to clarify whether targeting the quit date to the follicular or luteal phase of the menstrual cycle can improve smoking abstinence.

**Methods:**

Participants will enroll in an online smoking cessation program providing nicotine replacement therapy (NRT) and behavioral support. We will randomize 1200 eligible individuals to set a target quit date: (1) during the mid-luteal phase, (2) during the mid-follicular phase, or (3) 15–30 days after enrollment with no regard to the menstrual cycle phase (usual practice). Participants will receive a 6-week supply of combination NRT consisting of a nicotine patch plus their choice of nicotine gum or lozenge. Participants will be instructed to start using NRT on their target quit date. Optional behavioral support will consist of a free downloadable app and brief videos focusing on building a quit plan, coping with cravings, and relapse prevention, delivered via e-mail. Smoking status will be assessed via dried blood spot analysis of cotinine concentration at 7 days, 6 weeks, and 6 months post-target quit date.

**Discussion:**

We aim to overcome the limitations of previous studies by recruiting a large sample of participants and assigning target quit dates to the middle of both the follicular and luteal phases. The results of the trial can further elucidate the effects of the menstrual cycle on smoking cessation outcomes and whether it is beneficial to combine menstrual cycle phase timing strategies with accessible and low-cost NRT.

**Trial registration:**

ClinicalTrials.gov NCT05515354. Registered on August 23, 2022.

**Supplementary Information:**

The online version contains supplementary material available at 10.1186/s13063-023-07196-1.

## Introduction

### Background and rationale {6a}

Tobacco use is a risk factor for at least 20 types of cancer [1] and remains the leading preventable cause of cancer in Canada [2]. In 2015, an estimated 15% of all cancer diagnoses in Canadian women were attributable to active tobacco smoking, including 69% of lung cancer cases and 26% of cervical cancer cases [2]. Thus, smoking cessation is an important cancer prevention strategy for the close to 2 million Canadian women who currently smoke [3]. Although quitting smoking at any age is beneficial, women who quit smoking before age 45 avoid approximately 90% of lung cancers and overall mortality seen among continuing smokers [4, 5].

Although 45% of all smokers in Canada report making at least one quit attempt in the past year, 88% of these quit attempts are unsuccessful [6]. Evidence from both controlled trials and real-world clinical settings indicate that women have even greater difficulty achieving abstinence following a quit attempt than men [7, 8]. Our research group recently conducted a secondary analysis of data from 27,601 participants enrolled in our Smoking Treatment for Ontario Patients (STOP) program that confirmed significantly lower quit success in women undergoing smoking cessation treatment compared to men (24% vs. 27%) [9]. On a population level, this percentage difference translates into thousands of Canadian women continuing to accrue the risk of developing cancer and other smoking-related diseases. Thus, strategies are needed to increase the effectiveness of smoking cessation treatment for women to decrease the occurrence of preventable cancers and premature mortality.

In our STOP program, which provides up to 26 weeks of nicotine replacement therapy (NRT) personalized to individual needs, we found that associations between quit success and sex were not modified by the formulation, dose, and duration of NRT received. Additionally, the difference was independent of other confounding variables such as health and sociodemographic factors [9]. Thus, although women using NRT had lower overall quit success than men, variations in the type or duration of NRT received neither strengthened nor diminished this association between gender and quit outcome. This finding suggests that other factors, such as hormonal changes, need to be prioritized to help women using NRT achieve similar levels of quit success as men.

Individuals with a naturally occurring menstrual cycle experience changes in ovarian hormone levels, estrogen, and progesterone, across menstrual cycle phases. There is increasing evidence for the contribution of fluctuating ovarian hormones to the greater difficulty that women experience when trying to quit smoking [10]. As such, targeting quit date to the menstrual cycle phase could be a simple and effective strategy to improve smoking quit outcomes among premenopausal individuals.

In this study, we will test targeting initiation of a quit attempt assisted with NRT to specific phases of the menstrual cycle with a sample of premenopausal individuals. We hypothesize that starting a quit attempt during the follicular phase will result in increased quit success compared to starting during the luteal phase or the usual practice of not targeting quit start date to a menstrual cycle phase.

#### Clinical data supporting study interventions

A systematic review of menstrual cycle effects on nicotine withdrawal and craving following smoking cessation found that significantly greater withdrawal, and a trend for greater craving, was reported by women during the luteal phase compared to the follicular phase of their menstrual cycle [10]. In a pilot study of 35 female smokers who made a quit attempt with the aid of nicotine patch and counseling, those randomized to quit during their follicular phase (high estrogen) vs. luteal phase (high progesterone) had higher rates of abstinence 2 weeks after their quit date (32% vs. 19%), although the difference was non-significant [11]. Similarly, a second study [12] of 102 women receiving 8 weeks of NRT plus behavioral support found significantly higher quit rates on day 3 of treatment (81% vs. 48%) and 1 week after the end of treatment (69% vs. 29%) among women who set their quit date during the follicular phase versus the luteal phase. However, another study found rising progesterone levels (highest during the luteal phase) were associated with a 37% increase in odds of abstinence for the group that received nicotine patch (*n* = 56) [13]. These findings suggest that ovarian hormones and the menstrual cycle phase have an impact on NRT-aided quit outcomes. However, evidence for the influence of the menstrual cycle phase on smoking cessation outcomes have been limited by small samples and a lack of clarity surrounding ideal quit date timing. Therefore, we plan to conduct an adequately powered, rigorously designed study to clarify whether targeting quit date to the follicular or luteal phase of the menstrual cycle improves quit success*.*

#### Risks and benefits of study interventions

Regardless of which group a participant is assigned to, the study intervention will increase participants’ chances of successfully quitting smoking. Quitting smoking is the single most effective thing one can do to decrease their risk of preventable disease and death. NRT, such as nicotine patches, gum, and lozenge, is available over the counter in Canada because the risks of using NRT are minimal. The most common side effect of the nicotine patch is itchiness and redness at the site of the patch application. The most common side effect of nicotine gum or lozenge is upset stomach from swallowing the nicotine rather than letting it absorb through the buccal mucosa.

### Objectives {7}

The *primary objective* of this study is to determine whether targeting the quit date to either the luteal or follicular menstrual cycle phase improves short-term quit outcomes (7 days post-target quit date) compared to a self-selected target quit date without regard to the menstrual cycle phase (usual practice) for premenopausal persons provided with NRT and behavioral support to quit smoking.

The *secondary objectives* are (1) to determine whether there is a difference in short-term quit outcomes (7 days post-target quit date) between the groups targeting quit date to the follicular versus luteal phase of the menstrual cycle and (2) to identify any group differences in quit outcomes at the end of treatment (6 weeks) and 6-month follow-up.

### Trial design {8}

The study design is an open-label, parallel-group, superiority randomized controlled trial. Participants will be randomized into three groups in a 1:1:1 allocation ratio: (1) quit smoking during the mid-luteal phase of their menstrual cycle (6–8 days pre-onset of menses), (2) quit smoking during the mid-follicular phase of their menstrual cycle (6–8 days post-onset of menses), or (3) quit smoking 15–30 days post-enrollment with no regard to the menstrual cycle phase (usual practice). All participants will receive 6 weeks of NRT to aid in their quit attempt. The expected duration of the clinical trial is 48 months; we expect participant recruitment and data collection to occur over 27 months. Participants are not required to make any in-person visits; therefore, any potential COVID-19 restrictions are not expected to cause any significant disruptions to our timeline.

## Methods: participants, interventions, and outcomes

### Study setting {9}

The study will be conducted at Nicotine Dependence Services (NDS) at the Centre for Addiction and Mental Health (CAMH) in Toronto, Canada. Notably, this study is an Internet-based trial, and all interactions with study participants, including collection of informed consent, delivery of study instructions, baseline, and follow-up assessments, will be conducted virtually using Research Electronic Data Capture (REDCap) [14], a partner platform operated by CAMH, as well as via email and phone/text communication.

### Eligibility criteria {10}

#### Inclusion criteria

The study will recruit 1200 treatment-seeking naturally cycling individuals within Ontario, with a regular menstrual cycle (defined as cycle length ranging from 21 to 35 days over the past 6 months) aged 18 to 40 years. Eligible individuals must smoke at least 5 cigarettes per day over the past 6 months, be willing to quit smoking using NRT (nicotine patches and nicotine gum or lozenge) within 30 days and to make a quit attempt on their assigned target quit date, be willing to comply with study procedures (including providing dried blood spots), and provide a valid e-mail address to receive essential study communication and invitations to complete follow-up questionnaires.

#### Exclusion criteria

Individuals will be excluded from the study if they meet at least one of the following criteria: currently using progesterone, estrogen, testosterone, or fertility treatment; currently using NRT or other smoking cessation medications (e.g., varenicline, bupropion, cytisine); have used hormonal contraceptives in the past 6 months (e.g., pill, patch, hormonal intrauterine device [IUD], ring); are pregnant or trying to become pregnant within the next 3 months; have known hypersensitivity or allergies to any of the components of the nicotine patch; have used cannabis daily or almost daily in the past 30 days; have used tobacco or nicotine products other than cigarettes (e.g., smokeless tobacco, heat-not-burn products, e-cigarettes) daily or almost daily in the past 30 days; were diagnosed with polycystic ovary syndrome; have an unstable psychiatric condition (including substance use disorder) which would compromise study compliance; suffer from life-threatening arrhythmias or severe/worsening angina pectoris; experienced myocardial infarction or cerebral vascular accident in the past 2 weeks; or were diagnosed with a terminal illness.

### Who will take informed consent? {26a}

As this study is an Internet-based trial, participants will document their informed consent independently using a modified REDCap e-Consent Framework [15]. When potential participants indicate their interest in the study, they will be directed to read the consent and explore the FAQ website page related to the informed consent and the study. Potential participants will also be provided with study contact information (email address and phone number) and encouraged to reach out to discuss the study consent and ask any questions. They will be advised not to provide their consent until all their questions have been answered to their satisfaction.

### Additional consent provisions for collection and use of participant data and biological specimens {26b}

Consent on the use of data in ancillary studies is provided with the informed consent for the study.

### Interventions

#### Explanation for the choice of comparators {6b}

The usual practice was selected as the comparator condition in order to detect whether the anticipated benefit of targeting quit date to a particular menstrual cycle phase produces better quit outcomes than the current practice. Although targeting quit date to the follicular phase may lead to greater quit success than targeting quit date to the luteal phase (or vice versa), a benefit over usual practice is needed to support a change in the current treatment approach.

#### Intervention description {11a}

Participants will enroll in an online smoking cessation program providing NRT and behavioral support. Participants will receive a 6-week supply of NRT consisting of a nicotine patch plus their choice of nicotine gum or lozenge, which they will be instructed to start on their target quit date. Participants will be randomized to set a target quit date: (1) during the mid-luteal phase of their menstrual cycle (6–8 days pre-onset of menses), (2) during the mid-follicular phase of their menstrual cycle (6–8 days post-onset of menses), or (3) 15–30 days post-enrollment with no regard to the menstrual cycle phase (usual practice). We are allowing 14 days for the delivery of the NRT package. Hence, the earliest target quit date that a participant can have is at 15 days post-enrollment. Depending on the group they are randomized to, some participants may need to wait until their next cycle to start their quit attempt. Target quit date windows for all participants will be calculated in accordance with their menstrual cycle information (start date of last period and usual cycle length) and their enrollment date. Behavioral support will consist of a free downloadable app (My Change Plan) and brief videos delivered via e-mail. These videos have been produced by the CAMH NDS and will focus on health behavior change strategies, such as building a quit plan, coping with cravings, and relapse prevention [16].

The research team will mail each participant a study kit consisting of a 6-week supply of NRT (patches plus gum or lozenge) and dried blood spot collection kits. Participants who smoke 10 or more cigarettes per day will receive 4 weeks of 21 mg and 1 week each of 14 mg and 7 mg nicotine patches, while those smoking 5–9 cigarettes per day will receive 4 weeks of 14 mg and 2 weeks of 7 mg nicotine patches. Nicotine patches will be pre-organized into weekly packages, requiring the participants to reduce the dosage from 21 mg or 14 mg to 7 mg throughout the 6-week treatment period. All groups will be instructed to collect a dried blood spot and start using their NRT on their target quit date, as well as attempt to be completely abstinent from smoking starting from their target quit date onwards. Dried blood spots will be used to measure blood cotinine levels to confirm participants’ smoking status. Participants will be instructed to apply a new patch every day and use 2 mg nicotine gum or lozenge as needed to curb any urges to smoke. The research team will provide each participant with 2 packs of nicotine gum in which the maximum dosage is 30 pieces a day. These combinations and dosages of NRT have been found most effective for smoking cessation [17].

Participants will also have access to the behavioral support videos and handouts from the time they receive their welcome e-mail until the end of the study. Participants will be asked to complete daily diaries and weekly questionnaires to document tobacco use, NRT use, nicotine craving and withdrawal symptoms, mood, adverse events, and menstrual cycle symptoms via online REDCap surveys. Additional questionnaires will include Patient Health Questionnaire [18] (PHQ-9; weeks 1 and 6), Positive Affect and Negative Affect Schedule – Short Form [19] (PANAS-SF; weeks 1–6), Minnesota Nicotine Withdrawal Scale [20] (MNWS; weeks 1–6), and Perceived Stress Scale 4 [21] (PSS-4; weeks 1–6). Smoking status will be assessed at the end of weeks 1 and 6; those who self-report continuous abstinence from smoking for at least 7 previous days will be asked to collect dried blood spots and mail them within 3 days of collection (for biochemical verification of abstinence). At the end of treatment (week 6), participants will also be asked to complete a study satisfaction survey. Refer to Fig. 1 for a brief overview of the study and to Fig. 2 for a detailed schedule of events.

**Fig. 1 Fig1:**
[figure not shown]
Flow diagram for study events

**Fig. 2 Fig2:**
[figure not shown]
Schedule of study events for each participant (SPIRIT figure)

#### Criteria for discontinuing or modifying allocated interventions {11b}

Participants are free to discontinue the study intervention at any time. The study team will be able to identify the discontinuation when a participant does not complete follow-up surveys.

NRT is an over-the-counter product with a demonstrated safety profile. Therefore, we anticipate that the risk to participant safety will be minimal. However, participants may experience adverse events that can affect their decision to complete the intervention. The most common side effect of the nicotine patch is rash at the site of the patch application. This reaction can be quite pronounced in some people and may preclude their continued use of the patch. Other side effects include sleep disturbance and signs of nicotine toxicity. In case of severe sleep disturbance, it is recommended that participants take the patch off for 1–2 h before bed. If a participant is experiencing signs of nicotine toxicity, they are instructed to take the patch off for a few hours, switch to patches with lower nicotine content, or use nicotine gum/lozenge less frequently. Regardless, participants will be told to stop using the NRT if they experience adverse events that are not acceptable to them. The participants can still use nicotine gum or lozenge to aid in their quit attempt as well as the behavioral resources. We will ask participants to report their daily NRT use or non-use. We do not anticipate any systematic differences in the discontinuation of the intervention among the 3 groups since the intervention is the same for all groups.

#### Strategies to improve adherence to interventions {11c}

Daily diaries and weekly questionnaires will be programmed for automatic delivery in REDCap, based on the target quit date of the participant. Participants will also be notified about their target quit date and receive reminders to complete their baseline assessments, daily diaries, and weekly questionnaires. Reminders and notifications will be sent via email and/or SMS texts. If a participant does not provide information pertaining to the primary outcome of the study (quit status on day 7), the study staff will attempt to follow up with them.

As an incentive to complete and mail back dried blood spot collections, we will compensate participants with a $5 e-gift card for each dried blot spot collection received. Thus, all participants are eligible to receive at least one $5 e-gift card (baseline assessment) and can receive up to a total of $20 in e-gift cards throughout the study (up to 4 blood spots can be collected depending on whether participants achieve abstinence from smoking).

#### Relevant concomitant care permitted or prohibited during the trial {11d}

The screening questionnaire asks participants about the use of smoking cessation medications (e.g., varenicline and bupropion) that exclude them from participating in the study. Participants are also invited to disclose any medication use at baseline and week 6.

#### Provisions for post-trial care {30}

The interventions are designed to inflict minimal to no harm. If a participant is not successful in quitting within the study period and would like to explore other options for assistance with quitting, they may be directed to other CAMH programs and services, such as the Nicotine Dependence Clinic and STOP on the Net program.

### Outcomes {12}

#### Primary outcome

We are primarily interested in the between-group comparison of proportions of biochemically confirmed abstinence, measured through dried blood spots, at 7 days post-target quit date. The trial will be considered successful if the proportion of abstinent participants in either of the groups with a target quit date based on the menstrual cycle phase (follicular or luteal) is significantly higher than in the usual practice group.

#### Secondary outcomes

The secondary outcomes of the study are potential differences in proportions of biochemically confirmed abstinence (1) between the two intervention arms targeting quit date to menstrual cycle phase at 7 days and (2) between the two intervention arms targeting quit date to menstrual cycle phase and usual practice at 6 weeks and 6 months post-target quit date.

### Participant timeline {13}

#### Informed consent, screening, and baseline assessment

Following direct or self-referral to the study, potential participants will be provided with detailed study information and will be asked to provide informed e-consent. Participants will then be asked to complete a screening questionnaire to determine eligibility, and those who are eligible will be automatically directed to complete a baseline assessment to collect additional background information (e.g., sociodemographic, tobacco use history) and a contact information questionnaire to collect the participant’s mailing address, email, and phone number.

#### Randomization and study instructions

Enrolled participants will be randomized to one of three groups (*n* ~ 400 per group). A welcome email will inform participants of their target quit date range and ask them to inform study staff of their planned quit date (within the range) and begin their NRT on this date. The email will also provide instructions on how to use the NRT and dried blood spot kits and will contain Purolator shipment tracking information to track the delivery of the study kit. The email will also provide information about the online daily diaries, weekly questionnaires, and the 6-month follow-up questionnaire. Lastly, the email will include a link to the behavioral support resources and handouts.

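### Outcomes are timed from a quit date chosen after randomisation, with no anchor date for participants who report none, so loss before that date could differ by arm and fall out of the comparison

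*Protocol article*

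**What the plan says.** **How the date arises.** Under Randomization and study instructions, the welcome email gives each randomised participant a range and will "ask them to inform study staff of their planned quit date (within the range) and begin their NRT on this date". Objectives {7} calls the usual-practice date self-selected. The Inclusion criteria describe something different: willingness "to make a quit attempt on their assigned target quit date".

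**The ranges and the wait.** Intervention description {11a} gives the luteal arm days 6–8 before menses, the follicular arm days 6–8 after its onset, and usual practice days 15–30 after enrolment. To allow for delivery, "the earliest target quit date that a participant can have is at 15 days post-enrollment". The same section says that, depending on the group, some participants may have to wait for their next cycle, and that the study calculates the window for every participant.

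**What runs from the date.** The primary and secondary outcomes {12} are set at 7 days, 6 weeks and 6 months after the target quit date. Section {11c} has diaries and weekly questionnaires "programmed for automatic delivery in REDCap, based on the target quit date of the participant".

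**What happens to people without data.** Section {20c} expects under 5% missing for the primary outcome because of daily contact in the treatment phase. Section {18b} withdraws participants who fail to complete the week 1 and week 6 questionnaires and any required blood spots, and does not retain their data.

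**The concern.** The zero point of every endpoint depends on something the participant does after randomisation. Someone who loses interest during the wait, or never answers the email, has no stated day 7. Such a person cannot complete week 1 and week 6 items that have no date, and so can meet the non-adherence definition in {18b} and be removed.

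Failing to commit to a date is one way in which a timing strategy can fail. If those participants leave the data, the primary comparison is between people who accepted a date, not between the groups as randomised. The arms differ in exactly the features that could affect this, namely the width of the range and the length of the wait. Section {11b} expects no systematic difference in discontinuation because the intervention is the same in all groups, but the range and the wait are not the same.

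**Working it through.** **1. The plan's own figure.** Inputs from Sample size {14}: 400 per arm, 25% against 34%, 80% power. Two-sided alpha of 0.05 is assumed, since the sidedness is not stated. With a pooled, unadjusted two-proportion test:

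- mean proportion 0.295; SE under the null = √(0.295 × 0.705 × 2/400) = 0.0322
- SE under the alternative = √((0.25 × 0.75 + 0.34 × 0.66)/400) = 0.0321
- power = Φ((0.09 − 1.96 × 0.0322)/0.0321) = 79.8%

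The stated 80% is reproduced. By the plan's own statement it includes no allowance for attrition.

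**2. Range lengths.** Phase arms: 8 − 6 + 1 = 3 days. Usual practice: 30 − 15 + 1 = 16 days.

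**3. Waits.** Assume that enrolment is spread evenly over the cycle and that the centre of the phase window must fall on day 15 or later. For cycle length L the wait to the centre then runs from 15 to 14 + L days, with mean 15 + (L − 1)/2. The share beyond day 30 is (L − 16)/L. The Inclusion criteria allow L from 21 to 35.

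| Cycle length | Wait, range | Mean | Centre after day 30 |
|---|---|---|---|
| 21 | 15–35 | 25.0 | 5/21 = 24% |
| 28 | 15–42 | 28.5 | 12/28 = 43% |
| 35 | 15–49 | 32.0 | 19/35 = 54% |

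Usual practice waits 15–30 days, with mean 22.5 if dates are chosen evenly. Exposure to loss before the quit date therefore differs by design. The Inclusion criteria ask only for willingness to quit within 30 days.

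**4. What dropping non-setters would do.** The documents give no rate of non-setting, so these rates are assumed. Suppose there is no true effect (25% abstinent among all randomised in both arms), every non-setter smokes, and every non-setter is dropped. The observed proportion in an arm is 0.25/(1 − share not setting a date).

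| Not setting a date: usual practice / phase arm | Observed | Spurious difference | Two-sided rejection rate |
|---|---|---|---|
| 5% / 5% | 26.3% / 26.3% | 0.0 points | 5.0% |
| 5% / 10% | 26.3% / 27.8% | +1.5 | 7.3% |
| 5% / 15% | 26.3% / 29.4% | +3.1 | 15.3% |
| 5% / 20% | 26.3% / 31.3% | +4.9 | 30.2% |
| 10% / 5% | 27.8% / 26.3% | −1.5 | 7.3% |
| 15% / 5% | 29.4% / 26.3% | −3.1 | 15.3% |

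A milder assumption is 25% abstinence among setters and 5% among non-setters. The bias is then 0.20 × the difference in non-setting rates. For 10% in a phase arm and 4% in usual practice, the true values are 0.90 × 25 + 0.10 × 5 = 23.0% and 0.96 × 25 + 0.04 × 5 = 24.2%. Both arms are observed at 25%, so 1.2 points are hidden.

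**The case against.** The strongest reply is that this is a condensed article and that a default-date rule may stand in the full protocol. The study calculates the windows itself and notifies participants of their target quit date ({11c}), which fits a date held by the study and refined by the participant. Staff pursue missing day-7 status. Section {20c} plans extreme missing-data scenarios, a calculation of the group-by-missingness interaction that would overturn a significant result, and multiple imputation once 10% or more of the baseline sample is excluded. Unequal ranges are also part of the design, because usual practice means a self-selected date.

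Much of this stands. The unequal ranges are not a fault in themselves, and silence about a default date would be weak evidence alone. The safeguards do not close the gap, however. Chasing day-7 status needs a day 7. Daily contact during treatment does not cover the period before it. The rule in {18b} is an explicit instruction to discard data, and the {20c} analyses need those participants to remain in the dataset.

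A reader might also infer four stronger points that the documents do not support:

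- *The clock starts only when the participant reports a date.* No section says so.
- *Postponing the attempt moves follow-up.* Outcomes run from the target date, so a late attempt does not shift them, and no section provides for re-dating.
- *Day 7 may leave the assigned phase through rescheduling.* Phase defines the quit date, not the assessment. Seven days after a date 6–8 days before menses is already about the onset of menses.
- *The bias favours phase targeting.* That requires more non-setters in the phase arms. A 16-day open choice could produce more of them in usual practice.

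**Conclusion.** The point holds as a gap in how outcomes are anchored and participants retained, not as a demonstrated bias. As written, a randomised participant who reports no date has no stated anchor for any endpoint, lies outside the reasoning behind the under-5% expectation, and can be removed under {18b}. The Inclusion criteria and the randomisation section also describe the date differently, as assigned in one and chosen in the other.

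The size is unknown. With the assumed rates above, a 5-point imbalance in non-setting gives about 1.5 points and a 10-point imbalance about 3.1 points, against a planned 9. The sign follows the direction of the imbalance, and equal non-setting gives no spurious difference. These figures assume that non-setters smoke and are dropped, and they use an unadjusted test where the plan specifies covariate-adjusted logistic regression.

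**What to change.** At randomisation, have REDCap record a default anchor date inside each participant's computed window, for outcome timing only. Replace it with the participant's chosen date if one is reported within the window before the window opens, and lock it after that. Trigger the day-7, week-6 and 6-month assessments from the locked date for every randomised participant, and record the actual quit-attempt date separately. Keep all randomised participants in the primary analysis. Reconcile the Inclusion criteria, {11a}, {11c}, Randomization and study instructions, and {18b}, so that they describe one date mechanism and no longer remove people who never set a date.

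The cost is a calculated field and protocol wording. Some surveys will reach people who have not yet tried to quit. Power may also fall, because the sample size has no allowance for this. If 25% and 34% apply only among date-setters and non-setters count as smoking, power is 76.9% with 5% non-setting in both arms, and 58.6% with 5% in usual practice and 10% in the phase arm. In the second case the as-randomised difference is itself smaller: 0.90 × 34 − 0.95 × 25 = 6.9 points.
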